## Abstract

**Background:**

Opioid overdose remains a leading cause of preventable death in the United States. Existing approaches to identify individuals at elevated risk rely on imprecise rule-based criteria that misclassify patients’ risk of this serious health outcome. Machine learning (ML) algorithms can help improve prediction performance and can be combined with electronic health record (EHR) interventions to reduce overdose risk.

**Objective:**

The Machine Learning Prediction and Reducing Overdoses With EHR Nudges (mPROVEN) clinical trial integrates a validated ML overdose risk model with behavioral economics–informed EHR nudges to test whether the combination improves evidence-based prescribing behaviors associated with lower overdose risk and, ultimately, reduces overdose among elevated-risk patients.

**Methods:**

mPROVEN is a pragmatic cluster randomized controlled trial conducted in primary care practices within a large multistate integrated health system. Eligible patients are adults (≥18 years) identified by the ML algorithm as having elevated overdose risk and seen at a primary care visit during the study period. Primary care practices serve as the unit of randomization and will be randomized into three arms: (1) usual care; (2) elevated risk flag only, where clinicians see a noninterruptive EHR flag indicating elevated overdose risk; and (3) elevated risk flag + nudges, in which active choice and accountable justification alerts are embedded within the EHR in addition to the elevated risk flag. The trial will enroll a target cohort of 800 patients for the primary analysis. The intervention period is 4 months (or until the study ends, whichever occurs later). The primary outcome is a 3‑point composite measure of safer opioid prescribing at 4 months, awarding 1 point each for active naloxone prescription, average opioid dosage of 50 morphine milligram equivalents per day or less, and absence of opioid-benzodiazepine overlap. Secondary outcomes include the composite outcome at 6 months, individual score components, and all-cause and overdose-specific emergency department or inpatient visits. Outcomes will be compared across study arms using an intention‑to‑treat approach with linear mixed‑effects models accounting for clinic-level clustering.

**Results:**

Funded by the National Institutes of Health, in June 2022, enrollment began on March 10, 2025. Enrollment for the primary analysis cohort (n=798) was completed in May 2025 with additional participants enrolled for secondary analyses through December 2025 (n=1662). Primary cohort analyses began in January 2026, and results are expected by mid-2027.

**Conclusions:**

The mPROVEN study is among the first pragmatic randomized controlled trials to integrate ML‑based opioid overdose risk prediction with behavioral nudges within a large health system EHR. By combining advances in data science and behavioral economics, the study aims to reduce opioid overdose risk in primary care using a scalable and low-touch intervention to address a high-priority public health issue.

**Trial Registration:**

ClinicalTrials.gov NCT06806163; https://clinicaltrials.gov/study/NCT06806163

**International Registered Report Identifier (IRRID):**

DERR1-10.2196/94007

## Introduction

Opioid overdose remains a leading cause of preventable death in the United States, with 54,743 opioid‑related deaths in 2024 [1]. The economic and societal burden of opioid use disorder (OUD) and fatal opioid overdose exceeds US $1 trillion annually, including health care expenditures, lost productivity, premature mortality, reduced quality of life, and criminal justice involvement [2].

Although health systems and other stakeholders have instituted multiple interventions to reduce patient risk of overdose [3,4], including promoting safer opioid prescribing and dispensing naloxone, such efforts face 2 noteworthy challenges. First, there are limited and poorly performing tools to help clinicians identify who is truly at risk of overdose, leading to imprecise and burdensome interventions that target an overly broad population [5,6] or fail to identify the high-risk individuals most likely to experience overdose. Second, even with more accurate identification of elevated-risk patients, highly effective strategies to change clinician therapeutic behaviors remain limited.

To address these challenges, our team previously developed and externally validated machine learning (ML) algorithms for overdose prediction. In an application in Medicare data, these algorithms identified more than 90% of overdoses among the top risk groups, whereas commonly used risk classifications such as the high opioid dose measure used by the Centers for Medicare and Medicaid Services missed 70% to 90% of individuals with an actual overdose [3,7,8]. However, even with more accurate risk prediction in clinical settings, prognostic information may not translate into clinical action because clinicians face workflow challenges, biases and clinical inertia, and other barriers [9,10]. Behavioral nudges, which are subtle changes to how choices are presented or how information is framed to influence behavior without restricting choice, can help facilitate action by clinicians [11-16]. One nudge strategy, the *accountable justification*, prompts clinicians to briefly document a rationale for a clinical decision, and it has increased evidence-based oncology prescribing, reduced unnecessary antibiotic use, and decreased opioid prescribing in prior studies [17-19].

The Machine Learning Prediction and Reducing Overdoses With Electronic Health Record (EHR) Nudges (mPROVEN) study combines more accurate ML risk prediction with behavioral nudges as a targeted intervention to improve prescribing practices associated with overdose risk and, ultimately, reduce overdose risk itself. We integrated a validated ML-driven opioid overdose risk prediction model into a large health system’s EHR to identify patients at elevated risk of opioid overdose. We will conduct a 3-arm pragmatic, cluster randomized controlled trial (RCT) among patients with an elevated predicted risk of overdose, delivering within the EHR risk information, active choice alerts, and accountable justification alerts to primary care providers who see elevated-risk patients.

## Methods

### Overview and Study Setting

We designed mPROVEN as a 3-arm pragmatic cluster RCT conducted in primary care practices within the UPMC health system. UPMC is an integrated health system that includes 181 primary care (internal medicine and family medicine) practices in urban and rural settings in western and central Pennsylvania, New York, and northern Maryland. All outcomes and measures will be obtained from the UPMC health system EHR (Epic). This project is registered at ClinicalTrials.gov (identifier: NCT06806163). This trial adheres to the CONSORT (Consolidated Standards of Reporting Trials) extension for pragmatic trials [20] and aligns with the Pragmatic Explanatory Continuum Indicator Summary 2 framework for pragmatic study design [21].

### ML Opioid Overdose Risk Prediction Model

The ML risk prediction model uses a gradient boosting algorithm to predict 3‑month overdose risk using EHR data (eg, demographic characteristics, diagnosis codes, prescription orders and fills, and clinical encounters) [7,8,11,22]. Eligible primary care patients (defined below) have a risk score calculated weekly, and those whose predicted risk exceeds a predefined threshold (ie, ≥92.5th percentile in the training cohort) are classified as elevated risk. Model fairness and calibration were evaluated during development and further confirmed during a 4-month silent testing period conducted in the background of the UPMC Epic system. To support clinician understanding of the algorithm, we created a “frequently asked questions” (Figure 1) document embedded in the clinical trial alerts that summarizes model details, misclassification rates, and key limitations in an accessible format.

**Figure 1 figure1:**
[figure not shown]
First page of the Machine Learning Prediction and Reducing Overdoses With Electronic Health Record Nudges (mPROVEN) frequently asked questions (FAQ) document.

### Description of Interventions: Elevated Risk Alert Flags and Behavioral Nudges

#### Elevated Risk Alert Flag

Clinicians in the intervention arms receive a clinical alert indicating that a patient is at elevated risk of opioid overdose. The “elevated risk flag” is a noninterruptive alert displayed in the “storyboard” section of the Epic EHR, where it is visible to clinicians during the encounter. Additional information becomes visible when the clinician hovers over the alert (Figure 2). The storyboard alert will be present at each encounter while the study is active if the patient continues to meet the elevated risk criteria.

**Figure 2 figure2:**

Machine Learning Prediction and Reducing Overdoses With Electronic Health Record Nudges (mPROVEN) storyboard alert (copyright Epic Systems Corporation 2026; reproduced with permission from the copyright holder).

#### Behavioral Nudges

In addition to the elevated risk flag, clinicians in the elevated risk flag and behavioral nudges arm can also receive 2 types of EHR-embedded behavioral nudges: active choice and accountable justification.

##### Active Choice Nudge (Naloxone Ordering Prompt)

The active choice nudge will prompt clinicians to prescribe naloxone when caring for an elevated-risk patient who does not have naloxone on their medication list and who has not had a naloxone order in the previous year. The alert (Figure 3) will appear whenever any prescription order is entered, with the default option to prescribe naloxone.

Clinicians have several options to address this alert: (1) select “Accept” to order naloxone, (2) toggle “Do Not Order” and select “Accept” to not order naloxone; (3) select “Pt declined” to document that the patient declined naloxone, (4) select “Dismiss” to have the order go away (it will reappear if the eligibility criteria are met at the next visit), or (5) select “Defer” to temporarily move the alert to the storyboard for 24 hours. If naloxone is not ordered and the clinician does not use the “patient declined button,” the alert will reappear when an order is placed again in another encounter.

**Figure 3 figure3:**
[figure not shown]
Machine Learning Prediction and Reducing Overdoses With Electronic Health Record Nudges (mPROVEN) naloxone prescription behavioral nudge (copyright Epic Systems Corporation 2026, reproduced with permission from the copyright holder).

##### Accountable Justification Nudges

The accountable justification nudges appear for elevated-risk patients in the intervention arm when clinicians perform any of the following prescribing actions in the EHR, which are associated with an elevated risk of overdose [23]: (1) initiate a new opioid prescription for a patient who has had no opioid prescribed in the previous year (Figure 4), (2) order an opioid dose greater than 50 morphine milligram equivalents (MMEs) based on Epic’s automated opioid dosage calculation (Figure 5), and/or (3) prescribe concomitant opioids and benzodiazepines when one medication is prescribed while the other remains active on their medication list (Figure 6).

**Figure 4 figure4:**
[figure not shown]
Machine Learning Prediction and Reducing Overdoses With Electronic Health Record Nudges (mPROVEN) new opioid accountable justification nudge alert (copyright Epic Systems Corporation 2026, reproduced with permission from the copyright holder).

**Figure 5 figure5:**
[figure not shown]
Machine Learning Prediction and Reducing Overdoses With Electronic Health Record Nudges (mPROVEN) high dosage accountable justification nudge alert (copyright Epic Systems Corporation 2026, reproduced with permission from the copyright holder).

**Figure 6 figure6:**
[figure not shown]
Machine Learning Prediction and Reducing Overdoses With Electronic Health Record Nudges (mPROVEN) opioid and benzodiazepine overlap accountable justification nudge alert (copyright Epic Systems Corporation 2026, reproduced with permission from the copyright holder).

These 3 justification nudges have parallel functionality. For each, clinicians are prompted to enter a brief rationale into the medical record explaining the prescribing decisions for these elevated-risk patients. Clinicians may also “dismiss” the alert for the encounter or “defer” it until later in the same encounter. If the clinician does not enter a justification or dismisses the alert, it will reappear at the next eligible encounter (eg, a subsequent visit where an opioid and benzodiazepine are coprescribed). If a justification is entered, the alert will remain silent for 3 months and reappear only if the patient meets the triggering criteria.

### Pilot-Testing of the mPROVEN Intervention

The pilot phase of mPROVEN study was conducted over a 2-year period and consisted of 3 sequential steps (Figure 7). This approach emphasized close partnership with end users and other stakeholders to guide prioritization and iterative development cycles with frequent updates. We partnered with human factors experts to draft the initial design of the nudges.

**Figure 7 figure7:**

Timeline and steps for the Machine Learning Prediction and Reducing Overdoses With Electronic Health Record Nudges (mPROVEN) silent and live testing.

To gather end user feedback on the nudge designs, we conducted 4 clinician focus group sessions centered on the nudges’ content, presentation, and workflow integration. Feedback from these sessions informed revisions to the nudge designs. After the revised nudges were programmed into an Epic test environment, we held 6 one-on-one usability sessions with clinicians using an iterative feedback process to refine the nudges’ interface and functionality. Following usability refinements to the nudge intervention based on early focus groups, we initiated a 4-month silent testing phase in which the nudges described above ran *in the background* of the EHR across all UPMC primary care practices for elevated-risk patients without being visible to clinicians. This phase allowed the research team to validate the technical performance of the nudges, monitor alert volumes by practice, and ensure that the data infrastructure for outcome measurement functioned as intended. After confirming operational readiness, we proceeded to a 4-month live testing phase in 2 primary care practices. During this phase, clinicians were exposed to the elevated risk flag and the nudges during patient encounters. We collected quantitative data on clinician engagement with the nudges and qualitative feedback through a round of interviews. Insights from the live testing phase were used to finalize the intervention and prepare for the launch of the clinical trial.

### Trial Design

UPMC primary care practices serve as the unit of randomization, and all clinicians within a randomized practice receive the intervention assigned to the practice (Figure 8 [20]). Practices will be randomized to three arms: (1) usual care; (2) elevated risk flag only, where clinicians see a noninterruptive EHR flag indicating that a patient meets the elevated risk threshold; and (3) elevated risk flag + nudges, where clinicians see the elevated risk flag plus active choice and accountable justification alerts embedded within the EHR.

**Figure 8 figure8:**
[figure not shown]
CONSORT (Consolidated Standards of Reporting Trials) [20] flow diagram of the Machine Learning Prediction and Reducing Overdoses With Electronic Health Record Nudges (mPROVEN) cluster randomized controlled trial across 181 primary care practices in the UPMC health system.

This design allows us to assess the incremental benefit of adding behavioral nudges to an elevated risk flag and compare each intervention with usual care. Elevated-risk patients are enrolled into the trial at the time of the first qualifying primary care visit when one of the trial alerts is triggered (or, if in the usual care group, when an alert would have been triggered).

### Study Participants and Enrollment

Patients are eligible for enrollment in the trial if they are aged 18 years or older, have had an opioid prescription in the prior year, have an office or telemedicine primary care visit at a participating practice, and are identified as being at elevated risk by the ML algorithm. Patients are excluded if they had a malignant cancer diagnosis in the prior year or are receiving hospice care; if individuals develop a new cancer diagnosis or receive hospice care after enrollment, they will no longer receive the intervention. Importantly, although model development was restricted to patients receiving an opioid prescription in the prior year, the algorithm generates accurate risk estimates regardless of whether a patient has an active opioid prescription at the time of risk scoring.

### Study Outcomes

All trial outcomes and measures will be derived from the UPMC health system EHR. Follow-up for each patient begins at the date of enrollment (first encounter of an elevated-risk patient with a practice clinician). The primary outcome will be assessed 4 months after each eligible patient’s first encounter during the study period. This 4-month period was revised from the originally planned 6-month outcome (which is now a secondary outcome) due to an unexpected EHR system transition in September 2025.

The primary outcome is a composite measure of 3 prescribing practices scored as a 3-point ordinal score (0-3) in which each component contributes 1 point. A higher score indicates prescribing patterns associated with a lower overdose risk. Patients receive 1 point for each of the following: (1) an active naloxone prescription, defined as a naloxone fill or order within the previous year; (2) an opioid dosage of less than 50 MME per day, calculated as the average daily MME over the preceding 7 days based on prescription fill data or order data; and (3) the absence of overlapping opioid and benzodiazepine prescriptions, defined as no concurrent opioid and benzodiazepine fills or orders within the last 28 days.

For components 2 and 3, individuals not receiving any opioid prescriptions receive 1 point for each of those components. A maximum composite score of 3 is achieved when a patient (1) has an active naloxone prescription, (2) is not receiving high-dose opioids (≥50 MME), and (3) does not have concurrent benzodiazepine and opioid prescriptions within the previous 28 days. We *hypothesize* that our intervention will result in safer prescribing behaviors among elevated-risk patients, reflected by higher composite scores. Because overdose events are relatively rare within the trial time frame, the study is not powered to detect differences in overdose outcomes as a primary end point. Therefore, we selected a composite of evidence-based prescribing practices that are shown to be associated with reduced overdose risk as the primary outcome (with overdose as one of several secondary outcomes) [23-29].

Our secondary outcomes include the composite outcome at the 6-month follow-up; each individual component of our primary composite outcome; and several health care use measures, including all-cause and overdose-specific emergency department or inpatient visits.

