#### Sample Size and Power

We performed a priori power calculations using a simulation study designed to mirror the trial structure. The simulation incorporated 99 practices (created by regrouping the original 181 practices by size) and accounted for an unforeseen Epic system change that limited the intervention period to 4 months rather than the initially planned 6-month intervention period. The simulation used a multivariable proportional-odds linear mixed model and assumed an average of 8 eligible high-risk patients per clinical practice (range 2-16 across 1000 simulations), an intraclass correlation coefficient of 0.01, an estimated rate of the outcome from pilot analyses, and an anticipated 1– to 8–percentage point improvement in the primary composite outcome distribution from the usual care to the elevated risk flag plus nudge intervention arms, which is the a priori primary comparison for the study (Table 1). With 181 practices and a total sample size of 800 patients, the trial is estimated to have 81.3% power (α=.05) to detect the anticipated effect size between the elevated risk flag + nudges and usual care arms adjusting for a 1% attrition rate due to the development of malignant cancer or transition to hospice care after enrollment.

**Table 1 table1:** Outcome distributions assumed for power simulations for outcomes at 4 months (n=800).

Outcome			Usual care (%)		Elevated risk flag (%)		Elevated risk flag + nudges (%)
Naloxone			12		17.3		20.7
No high dose			90		91.3		92.7
No benzodiazepine overlap			94		94.7		95.3

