Missing data are expected given the use of routinely collected EHR data and variability in clinical documentation and data completeness across practices. When applying the gradient boosting model to enrolled patients, missing predictor values are addressed using simple imputation procedures, with continuous variables imputed using median values and categorical variables imputed using mode values. The ordinal primary outcome will be computed from UPMC EHR data; however, some outcome components or covariates may have missing values. We will examine missing data patterns and compare baseline characteristics between participants with and without missing outcome data. When appropriate, we will implement multiple imputation with the fully conditional specification approach [33] or use joint modeling or shared parameter model approaches that simultaneously model the outcome and dropout or death as sensitivity analyses when appropriate.

Descriptive statistics will summarize practice-, clinician-, and patient-level characteristics by group. Statistical assumptions will be evaluated for each model, with corrective procedures applied when needed. Statistical significance will be determined using a 2-sided *P* value threshold of .05. Analyses will be conducted using SAS (version 9.4) and R (version 4.0.2; R Foundation for Statistical Computing).

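### The no-opioid points in the primary score carry no condition that the patient is alive or still observable at 4 months, so a death or departure can score 2 or 3

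*Protocol article*

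**What the plan says.** Under Study Outcomes the protocol article states that "All trial outcomes and measures will be derived from the UPMC health system EHR". The three components are read from records in look-back windows:

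- Naloxone: "defined as a naloxone fill or order within the previous year".
- Opioid dose: "calculated as the average daily MME over the preceding 7 days based on prescription fill data or order data".
- Opioid-benzodiazepine overlap: "defined as no concurrent opioid and benzodiazepine fills or orders within the last 28 days".

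For the second and third components, "individuals not receiving any opioid prescriptions receive 1 point for each of those components". The direction is stated too: "A higher score indicates prescribing patterns associated with a lower overdose risk".

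Two other places bear on patients who die or leave. Sample Size and Power allows a "1% attrition rate due to the development of malignant cancer or transition to hospice care after enrollment". Statistical Analysis expects some missing outcome components, plans to compare patients with and without missing outcomes, and offers multiple imputation or models that "simultaneously model the outcome and dropout or death as sensitivity analyses when appropriate". No section says when a dose or overlap component is missing and when it counts as no opioid.

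**The concern.** A patient who has died, or who no longer uses the health system, generates no orders and perhaps no fills. The average dose over 7 days is then zero and there is no overlap in 28 days, so both components are met. Naloxone looks back a year, so an order at the index visit still counts at 4 months. Such a patient scores 2 or 3 on a scale whose upper end is meant to indicate lower overdose risk. This would include a patient who died of an overdose.

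Imputation and joint models act on values flagged as missing. A component that defaults to 1 point is not flagged, so it is unclear that those methods would touch it.

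Bias in the arm comparison needs exits that differ by arm. That is conceivable here. The accountable justification alerts fire on orders above the dose threshold and on overlap, which are the prescribing patterns that lose points on these components, and the clinicians are unblinded. A low-scoring patient who leaves because of the intervention would move up the scale without any safer prescribing.

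**Working it through.** **Inputs from the article.** Score distributions for 0/1/2/3 (Table 1): usual care 0.7/13.2/76.2/10.1%; flag + nudges 0.5/8.9/72.7/18.1%. Each column sums to 100.2% and was rescaled to 100%. Total 800 patients, 1:1:1, about 267 per arm (264 after 1% attrition); intraclass correlation 0.01; average 8 patients per practice; two-sided .05.

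**Method.** Fit a common proportional-odds OR to the two distributions. With n patients per arm after division by the design effect, and p̄ the average of the two distributions, V = 2n(1 − Σp̄³)/12 and z = ln(OR)·√V. Power is Φ(z − 1.96). Two-sided rejection is Φ(z − 1.96) + Φ(−z − 1.96).

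**The plan's own figure.** The fitted OR is 1.77 (ln OR 0.569). With design effect 1 + 7 × 0.01 = 1.07, n = 266.7/1.07 = 249.2, V = 24.3, z = 2.81 and power is 80.1%. With 800/181 = 4.42 patients per practice the design effect is 1.034 and power is 81.4%. The stated 81.3% is reproduced closely, so the model is a fair basis for the rest.

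**What the rule is worth per patient.** At usual-care rates a patient already expects 0.90 + 0.94 = 1.84 of the two points. The rule lifts this to 2.00, a gain of 0.16. A 10-point difference between arms in such patients shifts the mean score by 0.10 × 0.16 = 0.016. The planned mean difference is 0.087 + 0.027 + 0.013 = 0.127, so this is about 13% of it.

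**Balanced exits (shares assumed).** With 5%, 10% or 15% of both arms scored by the rule, power moves from 79.7% (264 per arm, design effect 1.07) to 79.4%, 79.1% and 78.8%. The OR stays at about 1.77.

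**Unequal exits with no true effect (shares assumed).** Both arms start from the usual-care distribution, in which scores 0-1 make up 13.9%, or about 37 of 267 patients. There are 264 per arm, and the design effect is taken as 1.045, between the two values above. In the unrelated case, leavers are a random draw who then score 2, or 3 at the 12% naloxone rate. In the concentrated case, all excess leavers come from scores 0-1 and move to 2.

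| Excess exit, nudge arm | Who leaves | Share of those scoring 0-1 | Spurious OR | Two-sided rejection |
|---|---|---|---|---|
| 4.5% | unrelated to score | 4.5% | 1.04 | 5.3% |
| 10% | unrelated to score | 10% | 1.08 | 6.6% |
| 2% (about 5 patients) | only scores 0-1 | 2/13.9 = 14% | 1.11 | 7.6% |
| 3% (about 8) | only scores 0-1 | 3/13.9 = 22% | 1.16 | 11.1% |
| 4.5% (about 12) | only scores 0-1 | 4.5/13.9 = 32% | 1.27 | 19.6% |

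For the last row, n = 264/1.045 = 252.6, V = 21.8 and z = 0.235 × √21.8 = 1.10. Scores 0-1 fall from 13.9% to 9.4%, which equals the planned fall at that cut. The larger planned shift, however, is at score 3 (10.1% to 18.1%) and comes mainly from naloxone.

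**The case against.** The strongest reply is that the article never says the dead or departed are scored. Its missing-data paragraph expects missing outcome components and names dropout and death, and the operational rule may sit in an analysis plan that is not shown. A reader might infer from the scoring rule that deaths and departures are deliberately counted as success and that the missing-data methods have nothing to act on. The documents do not go that far. What they contain is an unconditional scoring rule, and a missing-data paragraph that does not say how the two fit together. The joint models are also conditional and are sensitivity analyses, so they would not protect the primary result.

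A reader might also infer that patients who obtain opioids elsewhere are scored as safe. That is undetermined: fills as well as orders are used, fill-only and order-only definitions are compared in sensitivity analyses, and the article does not say whether fills from outside prescribers are captured.

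Three further points stand. Crediting patients who truly stop opioids fits the trial's aim. Each component is also a secondary outcome, so a shift confined to dose and overlap would be visible. Overdose-specific visits are a secondary outcome and a safety board reviews the trial, so deaths would not go unseen. None of these stops a death from entering the primary score as 2 or 3.

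**Conclusion.** The point holds as a defect in a stated rule: absent records and stopped opioids are scored alike, with no condition on being alive or observable. The likely numerical effect is small. If exits are balanced or unrelated to score, the planned comparison barely changes. A material false-positive risk needs 14% to 32% of nudge-arm patients scoring 0-1 to leave in excess of usual care within 4 months, with no excess among anyone else. That is a stress case, and the article gives no exit rate with which to judge it. The case for correcting the rule for deaths does not depend on these figures, because a death cannot sensibly be read as safer prescribing.

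**What to change.** - State in the outcome definition that the no-opioid points apply to patients alive at the 4-month date.
- Do not score deaths by the prescribing rule. Report them by arm and run a sensitivity analysis with death as the lowest category, which keeps every enrolled patient in the comparison.
- Report by arm how many patients have no health-system encounter, order or fill after enrolment.
- Prespecify a sensitivity analysis that sets the dose and overlap components to missing for those patients, using multiple imputation and, as a bound, a less favourable imputation.
- Fix all of this before arm allocation is revealed. Under Randomization and Blinding, that happens only after the primary models are finalized.

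The missing-data version is better as a sensitivity analysis than as the primary one. It conditions on behaviour after randomization that the intervention may affect, it sets to missing some patients who truly stopped opioids and did not return, and standard imputation assumes missing at random where the worry is informative departure.

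The cost is some extra derivation and analysis work, and a source for vital status, which the article does not describe. Precision falls in the sensitivity analysis: if 5%, 10% or 15% of patients were simply missing, power would be about 77.7%, 75.5% or 73.0% instead of 79.7%.
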